This study aims to explore the associations between CMDs, including symptoms of anxiety and depression measured monthly using the 12-item General Health Questionnaire (GHQ-12), and indicators of physical activity recorded by wrist-worn fitness trackers among UK veterans. Garmin-derived metrics include steps, active minutes per day, HRV, stress levels, and overall activity patterns. In addition, the study seeks to examine the relationship between mental health and broader functioning factors, such as somatic symptoms, loneliness, and sleep, in relation to physical activation metrics (steps, active minutes per day, HRV, stress, and activity) obtained from fitness trackers. The primary outcome of interest is the change in GHQ-12 score from baseline (T0) to day 84 (T3) associated with the change in physical activity over the 3-month study period. The study also aims to assess the feasibility of using fitness trackers to enhance the prediction and management of CMDs among UK veteran populations, to inform the development of a potentially larger-scale initiative. Feasibility will be assessed through recruitment rate, retention rate, and data completeness of both watch-derived data and monthly questionnaire responses. By integrating objective physiological data with self-reported mental health measures, this work ultimately aims to support improved monitoring and intervention strategies for CMDs within the veteran population.

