#### Privacy and Confidentiality

The study will collect limited personally identifiable information (name, contact details, service number verification, address, and study entry date) solely for participant communication and study administration. Identifiable data will be held securely by King’s College London and Combat Stress, stored separately from the research dataset, with access restricted to authorized members of the research team as approved by the principal investigator. Personally identifiable information will be held for a period of up to 1 year after the study has been completed. All data processing will comply with the General Data Protection Regulation (GDPR; specifically, the GDPR 2018 Act of Parliament) and institutional data–governance policies. Wearable-derived data will be transferred from the Garmin Connect app to SyncRation, the approved secure research platform used at King’s College London, via encrypted protocols (Transport Layer Security/Secure Sockets Layer) and stored on access-controlled servers with encryption at rest. Systems used by the research team maintain audit logs of data access and changes, and operate within protected, segmented network environments to reduce security risk. Identifiable information is stored separately from research datasets, with linkage performed through pseudonymized study identifiers. Garmin does not have access to any identifiable research data. Nonidentifiable information will be held for a period of up to 7 years after the study has been completed (Figure 1).

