**Incentive to complete the final questionnaire**																											
	Thank you, plus instructions to unlink Garmin Connect from SyncRation (emailed)																									×	
	£10^g^ Amazon voucher (emailed)																									×	

^a^Recruitment will occur prestudy.

^b^DSM-5: Diagnostic and Statistical Manual of Mental Disorders, Fifth Edition.

^c^UCLA: University of California, Los Angeles.

^d^Continuous data collection from week 1 to week 12.

^e^HRV: heart rate variability.

^f^MH: mental health.

^g^£10=US $13.40.

A link to the baseline measurement questionnaire will be sent to the participants (Table 2, SyncRation email 2). This will include basic demographic information, weight, height, as well as psychometric measures of mental and physical health outcomes. Once the baseline questionnaire is complete, the following day will signify the start date of the study for the participant (Day 1). Participants will complete all monthly questionnaires about their mental and physical health via the online survey platform (Qualtrics). This survey link will be automatically emailed to participants on day 28 (T1), day 56 (T2), and day 84 (T3) of the study via SyncRation. All physiological study data will be collected automatically from the watch, via the Garmin Connect smartphone app. Participants will be emailed 2 reminders to complete each survey: 2 days and 1 week after the survey is first emailed. If the questionnaires remain uncompleted, participants will be called by the research team a further 2 times, 8 days and 10 days after the date the survey link was emailed. Those who still do not complete the survey will be emailed a final time to say they have been withdrawn from the study. Participants who do not complete the questionnaires will not receive the £10 (US $13.40) Amazon gift voucher, but they may opt to keep the Garmin watch. Participants who complete the questionnaires will be gifted their watch after study completion and will receive a £10 (US $13.40) Amazon voucher as a gesture of goodwill for taking part. Participants will be sent a thank-you email for their participation, which will include instructions for unlinking their Garmin Connect app from the SyncRation platform. Participants who do not unlink from SyncRation will be manually unlinked by a member of the research team through the SyncRation platform to ensure cessation of data collection beyond the study end date.

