Watches will be delivered to participants’ home addresses and posted in batches. Due to the geographical distribution of participants across the United Kingdom, devices will be received and set up at different time points, resulting in variation in individual study commencement dates (day 1). Study commencement is defined as the point at which the watch is successfully set up and linked to the SyncRation platform and baseline measures are completed. Following successful setup of the device and completion of the baseline questionnaire, participants will be emailed by the research team to mark the study commencement (day 1), and all participants will complete the same study schedule. The study schedule is illustrated in Table 2, which includes all data collection points and questionnaire measures. A selection of health and well-being questionnaires has been selected to enable assessment of participants' mental health and well-being. See Multimedia Appendix 1 for full questionnaire markup.

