#### Exploratory Modelling

The primary exploratory outcome is the change in GHQ-12 score from T0 to T3. Secondary outcomes include change in other questionnaire scores. Initial associations between wearable features and mental health outcomes will be examined using simple regression models to estimate effect sizes.

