## Results

Enrollment for the pilot phase was completed in December 2024, with all pilot study participants completing the study (n=5). Data collection for the main study commenced in February 2025 and concluded in October 2025. As of March 2026, 52 participants have been recruited, of whom 48 have completed the study procedure, and 4 have withdrawn from the study. Recruitment occurred between February 2025 and August 2025. Data analysis is scheduled to begin in January 2026, with results expected to be submitted for publication in May 2026.

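### Start dates are staggered within a February to August window, and the GHQ-12/activity change association has no calendar term, so its effect size may be partly seasonal

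*Protocol article*

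**What the plan says.** **Primary question.** The Introduction of the protocol article defines the outcome of interest as the "change in GHQ-12 score from baseline (T0) to day 84 (T3) associated with the change in physical activity over the 3-month study period". Exploratory Modelling repeats the outcome: "The primary exploratory outcome is the change in GHQ-12 score from T0 to T3".

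**Timing.** Follow-up is fixed in study days, with surveys sent on "day 28 (T1), day 56 (T2), and day 84 (T3". It is not fixed in calendar days. Study Schedule explains that batch posting and differing delivery and set-up times lead to differing start dates, "resulting in variation in individual study commencement dates (day 1", and then notes that everyone follows the same schedule. The Results section gives the calendar: "Recruitment occurred between February 2025 and August 2025", and "Data collection for the main study commenced in February 2025 and concluded in October 2025". Of 52 people recruited, 48 completed.

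**Model.** Under Exploratory Modelling, associations between wearable features and mental health outcomes are to be "examined using simple regression models to estimate effect sizes". Season, calendar time and start date appear in none of Wearable Feature Construction, Missing Data, Exploratory Modelling or ML Analysis. They are also absent from Strengths and Limitations.

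**Status.** The Statistical Analysis overview calls every analysis exploratory and says the results will inform a larger study.

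**The concern.** A schedule that is identical in study days is not identical in season. Someone who starts in February gains daylight and warmth over the 84 days, and someone who starts in August loses them. If season affects both how active people are and how they feel, start date is a common cause of both change scores in the primary regression. Taking change within a person removes stable differences between people. It does not remove a seasonal change whose sign depends on when that person began.

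At stake is the effect size. The article says the regressions are there to estimate effect sizes, and that the findings will inform a larger study. An association that is partly seasonal could be carried forward as though it were all a link between activity and mental health.

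**Working it through.** There is no figure in the plan to reproduce: the sample size rests on no power calculation, and the article gives no standard deviation, expected correlation or seasonal effect. The check has four steps.

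**1. Dates.** Day 84 is day 1 plus 83 days.

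- Day 1 on 1 February 2025 gives day 84 on 25 April.
- Day 1 on 1 August 2025 gives day 84 on 23 October.
- If data collection ended on 31 October (the article gives only the month), the latest day 1 that still reaches day 84 is 9 August.

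**2. Does the seasonal part of the change reverse sign?** Assume a yearly cosine of unit amplitude peaking on 1 July (day 182 of the year). With day 1 on day *d* of the year, the built-in change is

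c(d) = cos[2π(d + 83 − 182)/365] − cos[2π(d − 182)/365].

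For 1 February, d = 32: cos[2π(−67)/365] − cos[2π(−150)/365] = 0.41 − (−0.85) = 1.25 (from unrounded terms). The other starts follow in the same way:

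| Day 1 | Built-in seasonal change |
|---|---|
| 1 Feb | +1.25 |
| 1 Mar | +1.29 |
| 1 Apr | +0.99 |
| 1 May | +0.43 |
| 1 Jun | −0.26 |
| 1 Jul | −0.86 |
| 1 Aug | −1.24 |

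The sign reverses during May. Day length at an assumed latitude of 53°N shows the same pattern: about +5.7 h for a 15 February start, about 0 for a 10 May start, and about −5.7 h for a 9 August start.

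**3. What correlation could this produce?** Suppose there is no true activity/GHQ-12 link, and season raises activity while lowering GHQ-12 (a lower score is better). If season explains a share R²_A of the variance of activity change and R²_G of the variance of GHQ-12 change, the induced correlation is

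r ≈ −√(R²_A × R²_G).

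A simulation checked this with 48 participants, 20,000 runs per setting, and starts spread evenly from 1 February to 9 August. The adjusted column is the partial correlation after adding the seasonal term.

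| R²_A / R²_G (assumed) | Formula | Simulated mean r | Mean r, adjusted |
|---|---|---|---|
| 2% / 2% | −0.02 | −0.019 | 0.001 |
| 5% / 5% | −0.05 | −0.048 | 0.002 |
| 10% / 5% | −0.07 | −0.070 | 0.001 |
| 10% / 10% | −0.10 | −0.100 | 0.000 |
| 20% / 10% | −0.14 | −0.140 | 0.001 |
| 20% / 20% | −0.20 | −0.198 | 0.001 |

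The adjusted column is a best case, because the covariate was the same curve that generated the data. When all starts fell within about four weeks in February, the unadjusted mean r lay between −0.001 and 0.002 in every setting.

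**4. What does adjustment cost?** Residual degrees of freedom fall from 48 − 2 = 46 to 48 − 3 = 45. If season has no effect on GHQ-12 except through activity, the covariate explains nothing further, and the standard error of the activity slope grows by about √[1/(1 − R²_A)]. That is √(1/0.98) = 1.01 at 2% and √(1/0.80) = 1.12 at 20%.

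**The case against.** **Covariates belong to an analysis plan that is not shown.** The sentence on regression describes a first look at associations, *simple* may only mean uncomplicated, and no adjustment set of any kind is listed. This stands in part: the article does not exclude a seasonal term. But it does name the model, and it discusses both staggered starts and limitations without mentioning season. The point rests on that, not on missing detail alone.

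**The size is assumed.** This stands. The documents give no seasonal effect on activity or GHQ-12, and no individual start dates. Batch posting could cluster the starts, and the problem would then largely vanish.

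**A seasonal association is still an association.** For monitoring or prediction that is fair, and if season affects mood only through activity, the unadjusted slope is not confounded by it. In that case adjusting costs precision but adds no bias. This argues for showing both estimates rather than replacing one with the other.

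Two stronger readings are tempting, and the documents support neither.

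- A reader might infer an inflated false-positive rate. The article sets no significance level and plans no decision rule for this association; its stated aim is effect sizes. A rejection rate at 5% would describe a test that is not planned.
- A reader might infer that analysts cannot obtain start dates, because Privacy and Confidentiality lists the "study entry date) solely for participant communication and study administration" and keeps identifiers apart from the research data. The same section provides for linkage through pseudonymised identifiers. Sensor data must be dated to be aligned with T0 to T3, and Adverse Events shows the team already working with individual start dates. Nothing says that calendar time is stripped from the research dataset.

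**Conclusion.** The point holds as a gap in the analysis of an exploratory study. It is not a contradiction or a wrong figure. Start dates vary within a recruitment window of about six months, the seasonal part of an 84-day change can reverse sign across that window, and neither the named model nor the limitations allow for it. The primary effect size may therefore be partly seasonal.

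The documents cannot say by how much. The range of about −0.02 to −0.20 runs from negligible to material for planning. It depends on three assumptions: season explains 2% to 20% of the variance of each change score, it acts on activity and GHQ-12 in opposite directions, and starts are spread evenly from February to early August. With clustered starts the induced correlation is close to 0. The study's own data would help to show which case applies, and the present text does not ask them to.

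**What to change.** - **Exploratory Modelling:** report the primary GHQ-12/activity estimate with and without one seasonal covariate, either the change in day length from day 1 to day 84 or the start date. Choose the covariate before analysis. Day-length change follows the reversal of sign directly; a linear start date only approximates it.
- **Descriptive and Feasibility Analyses:** describe the distribution of start dates, for example by month, so that readers can judge how far the seasons differ between participants.
- **Strengths and Limitations:** add a sentence on season.

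No new data are needed, since study entry date is already collected. The cost is one degree of freedom at about 48 participants. If season acts mainly through activity, there is also some loss of precision, up to about 12% on the standard error at the top of the range considered.

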### Wearable Tracker

Garmin devices (Figure 2) are consumer-grade wearables widely used in health research. Existing validation studies have demonstrated acceptable accuracy for step counting, heart rate, HRV-derived indices, and sleep duration in free-living and laboratory conditions. While these metrics do not replace clinical gold standards, they are considered reasonable proxies for exploratory digital phenotyping studies and have been used in hundreds of published research projects [34]. The device is therefore suitable for feasibility work focusing on patterns of association rather than clinical diagnosis. For this study, the Garmin vívosmart-5 will be used. This device is Conformité Européenne marked and approved for sale and use in the United Kingdom. The device has a battery charge of 7 days and can store data for up to 2 months.

### Sensor Modalities

Sensors included a Garmin Elevate wrist heart rate monitor, Pulse Ox blood oxygen saturation monitor, accelerometer, ambient light sensor (for display brightness adjustment), device-generated values (sleep, stress, maximal oxygen consumption, and zero-crossing), and human-recorded events (activities and body composition; Table 3).

**Table 3 table3:** Garmin vívosmart-5 sensor modalities.

Data type	Variables/description	Sensor
Energy (body battery)	Composite energy score derived from physiological signals	Garmin device (algorithm-generated)
Heart rate	Resting heart rate; heart rate (beats per minute); beat-to-beat interval; heart rate variability	Garmin Elevate wrist heart rate monitor
Respiration	Respiratory rate summaries	Pulse oximeter
Sleep	Sleep score, sleep duration (hours), and sleep quality	Garmin device (algorithm-generated)
SpO_2_^a^	Blood oxygen saturation level	Pulse oximeter
Stress	Physiological stress score derived from heart rate variability	Garmin device (algorithm-generated)
Physical activity	Step count, active minutes, and self-reported activity	Accelerometer; actigraphy; self-reported (human-recorded events)

^a^SpO_2_: saturation peripheral oxygen.

Each smartwatch package includes the following items: Garmin vívosmart-5, USB-C charging cable, and user manual. Participants will be provided with the complete set, consisting of the device and all accompanying contents listed. Participants will be sent instructions on the proper handling and operation of the device. If requested, participants can arrange a video call with a member of the research team to support setup. The manufacturer of the watch, Garmin, will not have access to any study data. At the end of the study, participants can opt to retain the device or send it back to the research team via a prepaid postage box.

### Data Collection

During the study enrollment, participants will be required to download a smartphone app to facilitate data collection (eg, syncing data from the watch). Participants will download the mobile app Garmin Connect via the Apple Store or Google App Store on their personal mobile device. Participants will be required to consent to King’s College London accessing and processing their data via the SyncRation portal. SyncRation is a research-viable product developed by King’s College London to facilitate participant engagement and data synchronization [35]. Participants will be encouraged to synchronize data weekly and at the end of the study via the Garmin Connect app. Participants are able to withdraw at any time via SyncRation, without any need to contact the research team. The app does not collect any personal identifiers such as name, location, or date of birth. The research team will provide the participants with a user manual and guide them through the setup process to explain common features of the app. Once the data are synced, participants will be able to view their data on the Garmin Connect app interface. The research team will be contactable throughout the study to address any technical issues and provide guidance to participants on the use of the vívosmart-5, Garmin Connect app, and SyncRation platform. The research team will not review data in real time but will perform automated quality control checks to ensure data integrity.

### Recruitment

UK veterans will be recruited through convenience sampling methods. Social media posts on LinkedIn, Facebook, and Instagram will advertise the study via open adverts. In addition, veteran groups and peer support networks will be contacted via email and invited to participate in the study (eg, email distribution lists originating from veteran organizations), veteran charities will be contacted, and requests to advertise in relevant charity newsletters will be made. Once participants have successfully completed the eligibility survey and informed consent form, the research assistant will arrange a call with the participant to explain the study in depth, ensure sufficient English language skills, confirm veteran status via service number, and go through the participant information sheet. Participants will be given time to ask questions or raise any concerns. The research assistant will make it clear that participation is entirely voluntary, that participants are not under an obligation to participate, and can withdraw from the study at any time.

### Sample Size

This study is an observational feasibility study. As such, no power calculation has been performed. Research specifically within the UK veteran populations is limited; a sample of 30 was used in a feasibility study using wearable technology to predict PTSD symptoms and cannabis use among UK veterans [36]. Feasibility trials using wearable devices in community and veteran populations commonly recruit between 15 and 110 participants [37-39], and a recent US veteran wearable feasibility study successfully used a sample of 74 [40]. The selected sample size for this study is 50 veterans. A sample of 50 enables the study to estimate key feasibility outcomes, such as recruitment rate, retention, survey completion, and wearable data availability, with acceptable precision for planning a larger study. Although the machine learning (ML) component is exploratory, each participant contributes up to 84 days of continuous data, providing a significant amount of data [40]. In feasibility settings, ML analysis focuses on identifying whether wearable features show consistent signals and whether models can be trained without substantial overfitting, rather than producing validated prediction models.

### Adverse Events

Participation in this study is not expected to result in adverse events. Nevertheless, researchers will monitor changes in participants' mental health over the course of the study to ensure safety. Incoming GHQ-12 scores from participants' monthly surveys will be monitored on a weekly basis by the research team. Weekly monitoring will be conducted to account for participants’ different start dates and, therefore, different monthly questionnaire completion dates between participants, to ensure that safeguarding response procedures are initiated within a week of data collection. Any participants reporting an increase in GHQ-12 score of ≥15 points between 2 consecutive surveys will be contacted immediately by a member of the research team. During this contact, participants will be provided with the signposting booklet of veterans’ mental health services. If concerns about the participant’s well-being arise during this correspondence, the case will be escalated for further assessment. This will involve a call with a designated member of the research team. Further action required following confirmation of risk will result in a referral to the clinical lead (DM) to perform a clinical interview and risk assessment, and to determine whether and what additional support is required and whether the participant should be withdrawn from the study. All contact, assessments, and actions undertaken in response to potential adverse events will be documented, and any data collected before withdrawal will be used for analysis.

